#### Altering Dynamics of Autonomic Processing Therapy (ADAPT)

Expert collaborators recommended combining cognitive approaches from health psychology (targeting catastrophisation of internal sensations [22, 41, 42] with bio-behavioural training to reduce *autonomic trait prediction error* (i.e. to increase correspondence between measured changes in heart rate and subjective judgement of these changes). Cognitive behavioural principles will be used to address anxiety through structured sessions, problem identification, formulation and behavioural experiments. Sessions will focus on addressing beliefs and appraisals around anxiety and safety seeking behaviours, imagery rescripting and homework tasks to be completed between sessions adapted from (Clark, Salkovskis et al. 1999). Participants will be allocated to one of four protocols detailed below (Table 3). Therapists will review homework tasks with participants weekly to assess progress and intervention adherence. Interoception training will be conducted in five of the therapy sessions. Interoception training will be completed via a MATLAB platform on a laptop and will require participants to wear a pulse oximeter (NONIN), which will enable their heartbeats to be recorded. Interoception training will involve two tasks: heartbeat tracking and heartbeat discrimination [29]. In heartbeat tracking, participants will be asked to count their heartbeats across a period of time across 6 trials (range 10–50 s). Participants will start using ‘set B’ with trials in duration between 10 and 25 s. If the participants get 4 trials correct (within 3 beats of the actual answer), they change sets to ‘set A’ with trials 25–50 s in duration. If participants get 4 trials 5 beats or more out on set A, they reduce the next training set back to set B. In heartbeat discrimination, participants will be played their real heartbeat (10 beats); however, the task randomly introduces a delay of 300 ms in some of the trials. Participants will have to decide if the heartbeat they hear is in or out of sync with their actual heartbeat. Participants will complete 20 trials of the heartbeat discrimination task. After each trial, participants will be asked to make a confidence judgement on their response on a visual analogue scale ranging from 0 (not at all confident) to 100 (extremely confident). Participants will be informed after each trial the actual number of heartbeats in the trial or whether the tone was in or out of sync with their actual heartbeat. They will then exercise for 2 min to raise their heart rate and repeat both heartbeat tracking and heartbeat discrimination tasks.

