### Outcome

Anxiety is the primary outcome, which will be measured by the BAI and group comparisons of mean scores from baseline assessment to end of therapy will be made. Secondary outcomes are as follows: autonomic trait prediction error, interoceptive trait prediction error, presence or absence of psychiatric disorder measured by the MINI [27], the GAD-7 ([43] an additional anxiety measure), depression measured by the PHQ-9 [32], functioning measured by the Work and Social Adjustment Scale [33], anxiety sensitivity quantified by the Anxiety Sensitivity Index [35], alexithymia (i.e. difficulty describing one’s emotions) measured by the Toronto Alexithymia Scale-20 [36], dissociation quantified by the Dissociative Experiences Scale [37] and current panic symptoms measured by the Panic Disorder Severity Scale [38] (see more information on measurement in Table 4). All secondary outcome assessment (except the MINI and feasibility measures) will involve analysing change scores on the measures listed from baseline assessment to end of therapy. The MINI will involve comparing the number of psychiatric disorder presentations from baseline assessment to end of therapy. Trained clinical psychologists will complete psychological interview assessments (including the MINI) and a trained research assistant will complete research assessments.

**Table 4 Tab4:** Outcome measures

Level of outcome	Outcome measures
Primary outcome	Anxiety levels (BAI) [28]
Secondary outcomes	Autonomic trait prediction error (calculated by z- transforming the mean proportional rise in heart rate on active stand [orthostasis] and subtracting the z-transformed orthostatic sub-scale of the Autonomic Symptoms of Quality of Life Score [40] for each participant)

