	Interoceptive trait prediction error (i.e. the mismatch between objective interoceptive accuracy and subjective interoceptive sensibility [44]) will be calculated using the difference between interoceptive sensitivity (i.e. accuracy) and sensibility. Interoceptive sensibility and interoceptive sensitivity scores will be z-transformed and one subtracted from the other. Interoceptive sensitivity score will be calculated across the heartbeat tracking trials at assessment using this equation [44, 45]: $$ 1-\frac{\left|{\mathrm{nbeats}}_{\mathrm{real}}-{\mathrm{nbeats}}_{\mathrm{reported}}\right|}{\left({\mathrm{nbeats}}_{\mathrm{real}}+{\mathrm{nbeats}}_{\mathrm{reported}}/2\right)} $$ for heartbeat discrimination trials, this will be calculated by: number of correct trials / number of total trials in assessment Interoceptive sensibility will be assessed using the total score from the Body Perception Questionnaire [39].
	Presence/absence of psychiatric disorder as evidenced by the MINI [27]: Major depressive episode, panic disorder, agoraphobia, social anxiety disorder, obsessive-compulsive disorder, posttraumatic stress disorder and generalised anxiety disorder
	Psychiatric symptomatology as evidenced by scores on the: 1. GAD-7 [43] 2. PHQ-9 [32] 3. Work and Social Adjustment Scale [33] 4. Anxiety Sensitivity Index [35] 5. Toronto Alexithymia Scale-20 [36] 6. Dissociative Experiences Scale [37] 7. Panic Disorder Severity Scale [38]
	Feasibility and acceptability measures of RCT (e.g. practicability, tolerability, Satisfaction with Therapy questionnaire [46])

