### Sample size

Eighty is the required sample size. Based on previous experimental data (mean anxiety levels in hypermobile subjects BAI = 24.5 [sd 9.36]), this sample size is powered (90% power, 0.05 α) to detect a clinically meaning difference on BAI of 7.5 points (34 participants per group). Thirty-five people per group is the recommended sample size, based on estimating the standard deviation of the primary outcome with good precision [20], to obtain good quality data to inform planning of a future definitive trial. Studies conducted by [name] indicate an attrition rate of approx. 14%; thus, the sample size of 40 per group will take this into account. No further follow-up measures will be obtained if a participant withdraws from the study.

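### The heartbeat-tracking accuracy equation in Table 4 is very likely mis-bracketed: it halves only the reported count, and followed literally it raises and compresses the scores

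*Protocol article*

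**What the plan says.** The Outcome section of the protocol article names the measure among the secondary outcomes: "Secondary outcomes are as follows: autonomic trait prediction error, interoceptive trait prediction error". Table 4 builds it from two parts. It "will be calculated using the difference between interoceptive sensitivity (i.e. accuracy) and sensibility", and "Interoceptive sensibility and interoceptive sensitivity scores will be z-transformed and one subtracted from the other".

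The objective part is accuracy. For the tracking task, "Interoceptive sensitivity score will be calculated across the heartbeat tracking trials at assessment using this equation". The equation that follows is 1 minus a fraction. The numerator is the absolute difference between real and reported beats. The denominator reads, in its source markup, "nbeats}}_{\mathrm{real}}+{\mathrm{nbeats}}_{\mathrm{reported}}/2", and the bracket closes directly after the 2. By ordinary precedence this is real + (reported/2).

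Table 4 scores the discrimination task separately, as the proportion of correct trials, so that score is not affected. The tracking formula is not restated or corrected elsewhere in the article.

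**The concern.** A division by two in this position makes sense as part of a mean of the two counts. As printed, it gives the counts unequal weight without a stated reason, and it leaves an outer bracket that has no function in a denominator. Both features suggest that the bracket was closed in the wrong place.

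This is a scoring rule for a named outcome, so someone who codes from the article would reproduce it. The resulting accuracy scores would sit higher and closer together than those of the averaged form. The distortion is not a constant shift or a constant factor, so later standardisation cannot remove all of it. It also bears on change from baseline, which is how the Outcome section says this measure will be analysed. The article plans open release of anonymised data, so outside users might score from the same equation.

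**Working it through.** **Inputs.** Let r be real beats, p reported beats, and k = p/r. The article gives no accuracy value to reproduce, so the check evaluates the formulas directly.

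- Printed: P = 1 - abs(r - p) / (r + p/2)
- Averaged: M = 1 - abs(r - p) / ((r + p)/2)
- Plain proportional, as a second comparison: R = 1 - abs(r - p) / r

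**Direction.** The printed denominator exceeds the averaged one by (r + p/2) - (r + p)/2 = r/2, and it is never less than r. So P is never below M and never below R, and the direction does not depend on which of the two was meant.

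**Size with r = 40.**

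| Reported p | Printed P | Averaged M | Plain R | P - M |
|---|---|---|---|---|
| 0 | 0.00 | -1.00 | 0.00 | 1.00 |
| 10 | 0.33 | -0.20 | 0.25 | 0.53 |
| 20 | 0.60 | 0.33 | 0.50 | 0.27 |
| 30 | 0.82 | 0.71 | 0.75 | 0.10 |
| 36 | 0.93 | 0.90 | 0.90 | 0.04 |
| 40 | 1.00 | 1.00 | 1.00 | 0.00 |
| 50 | 0.85 | 0.78 | 0.75 | 0.07 |
| 60 | 0.71 | 0.60 | 0.50 | 0.11 |
| 80 | 0.50 | 0.33 | 0.00 | 0.17 |

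For example, p = 20 gives P = 1 - 20/50 = 0.60 and M = 1 - 20/30 = 0.33.

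**Unequal treatment of the counts.** Swap them to r = 20, p = 40. Then P = 1 - 20/40 = 0.50, against 0.60 before the swap. M = 1 - 20/30 = 0.33 both ways.

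**Effect on change, r = 40.**

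- From 10 to 20 reported: P gains 0.600 - 0.333 = 0.27 and M gains 0.333 + 0.200 = 0.53, a ratio of 0.50.
- From 20 to 30 reported: P gains 0.818 - 0.600 = 0.22 and M gains 0.714 - 0.333 = 0.38, a ratio of 0.57.
- Close to a perfect count, the printed divisor is about 1.5r and the averaged one about r, so the ratio approaches 2/3.

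The shrinkage therefore varies with the starting level.

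**After the z-transform.** Both scores depend only on k. For k below 1, P = 3k/(2 + k) and M = (3k - 1)/(1 + k). Both rise with k, so under-counters are ranked identically on a single trial. Ranks can differ once over-counters are mixed in: with r = 40, reporting 20 and reporting 80 tie at 0.33 under M but score 0.60 and 0.50 under P.

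A simulation sized this. All its inputs are assumptions: 20,000 people, six trials of 25 to 50 s, heart rate averaging 75 per minute, each person's k drawn uniformly from the range shown, and added trial noise. The article describes the tracking task for training, where "participants will be asked to count their heartbeats across a period of time across 6 trials (range 10–50 s"); it does not give assessment trial lengths. Because the scores depend only on k, trial length matters little here beyond rounding.

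| Range of k | Mean P / M | SD P / M | Correlation P, M | Largest z-shift |
|---|---|---|---|---|
| 0.2-1.0 | 0.67 / 0.43 | 0.21 / 0.38 | 0.9986 | 0.27 |
| 0.5-1.0 | 0.80 / 0.68 | 0.11 / 0.19 | 0.9996 | 0.28 |
| 0.5-1.3 | 0.84 / 0.75 | 0.10 / 0.18 | 0.9983 | 0.30 |
| 0.3-1.7 | 0.76 / 0.62 | 0.15 / 0.26 | 0.9884 | 0.50 |
| 0.2-2.5 | 0.64 / 0.47 | 0.20 / 0.30 | 0.9600 | 1.17 |

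If the z-transformed questionnaire score is also assumed independent of accuracy, the two versions of the difference score correlate (1 + c)/2, where c is the correlation in the table. At the lowest, (1 + 0.96)/2 = 0.98.

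**The case against.** The strongest reply is that this is a typesetting slip with little consequence, and much of that stands.

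- **The intended formula is inferred.** The article attributes the equation to cited sources that are not available here, and nowhere does it say that the counts are averaged. The redundant outer bracket is the best clue. Asymmetry alone is weak evidence, because the plain proportional form is asymmetric too. A score of 0 for no reported beats is not proof of error either, since the plain form also gives 0.
- **The large differences are in raw accuracy.** The listed outcome uses z-transformed accuracy, which removes most of the level and scale difference.
- **No bias between arms is shown.** The same equation would score both arms at both time points.

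A reader might infer that accuracy will in fact be computed wrongly and overstated in the trial. The documents do not support that, because no scoring code is shown and the code may already use the intended form. Three related inferences also fail:

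- that the error is divided by about 1.5 times the beat count for poor trackers. This holds only near a perfect count; at 20 of 40 the divisor is 50, or 1.25 times the real count;
- that the training is aimed at under-counters. Its stated criteria are distances from the true count and name no direction;
- that the HeartRater app supplies the assessment scores. The COVID-19 section describes it for training.

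What the reply does not remove is the printed rule itself. It defines an outcome, it is not corrected elsewhere, and followed literally it gives different scores from the form very likely meant.

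**Conclusion.** The point holds as a very likely mis-bracketed outcome definition of limited reach. That the printed score is never below the averaged or the plain form is algebra and needs no assumption. That the mean was intended is a strong inference from the bracket.

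Followed literally, raw tracking accuracy rises by 0.04 at a 10% under-count, 0.10 at 25% and 0.27 at 50% relative to the averaged form, and gains are cut to between about half and two thirds in the cases worked. For interoceptive trait prediction error the effect is small if participants mainly under-count (accuracy correlations of about 0.998 or higher). It is moderate if over-counting is common (0.96 to 0.99, with some individual shifts of 0.5 to 1.2 SD). Those figures rest on assumed counting patterns in a single cross-section; change by arm was not simulated, so no effect on a treatment comparison is claimed.

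The primary outcome and the sample size, which "this sample size is powered (90% power, 0.05 α) to detect a clinically meaning difference on BAI of 7.5 points" describes, do not use this formula.

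**What to change.** Check the formula against the sources cited in Table 4. If the mean of the two counts was intended, print the score as 1 - abs(real - reported) / ((real + reported)/2), averaged over the tracking trials. If another form was intended, print that form unambiguously. Then confirm that the code scoring the assessment tracking trials uses the same formula at baseline and end of therapy, and give that formula with any released data.

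The cost is one bracket in the outcome definition, a look at the source and a code check. No data collection, sample size or primary analysis changes.

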### Sample size

Eighty is the required sample size. Based on previous experimental data (mean anxiety levels in hypermobile subjects BAI = 24.5 [sd 9.36]), this sample size is powered (90% power, 0.05 α) to detect a clinically meaning difference on BAI of 7.5 points (34 participants per group). Thirty-five people per group is the recommended sample size, based on estimating the standard deviation of the primary outcome with good precision [20], to obtain good quality data to inform planning of a future definitive trial. Studies conducted by [name] indicate an attrition rate of approx. 14%; thus, the sample size of 40 per group will take this into account. No further follow-up measures will be obtained if a participant withdraws from the study.

### Recruitment

Participants will primarily be identified through ethically approved advert. Adverts will be displayed at clinical sites and distributed via electronic and paper messaging boards/newsletters to potential participants, e.g. research small ads at University of Sussex and Facebook/Twitter accounts/newsletters of relevant patient/research organisations (e.g. via Brighton and Sussex Medical School [BSMS] and partner universities, by funder (MQ: Transforming Mental Health), and by patient organisations (e.g. Hypermobility Syndromes Association, Ehlers-Danlos Support UK). Electronic advertisement will use geo-targeting to the Sussex and wider South East area where possible. Potential participants will also be identified using the Sussex Partnership NHS Foundation Trust Research Network.

All further contact with potential participants will be via phone, email and post as described below and per potential participant preference.

Interested participants responding to the advert will then contact the research team (email/phone) and be sent (email/post) an appropriate for phase PIS inviting them to contact the research team (email/phone) for further information. A trained member of the research team will then conduct a basic telephone screening to check if potential participants meet inclusion criteria for the study. Participants deemed eligible to take part in the study will subsequently be invited to take part in the study assessment by a study clinical psychologist. A trained research assistant or a member of the research team will collect informed consent from participants prior to undergoing assessment.

The research team will sensitively inform participants if they do not meet the criteria and give an explanation. They will be signposted to relevant support organisations as appropriate and reassured that their routine clinical care will not be affected in any way.

### Treatment allocation and blinding

Participants will be allocated to either ADAPT or EFST through the online randomisation service sealed envelope [47]. Minimisation with a random element (80% probability of being allocated to the arm which minimises imbalance) will be utilised, and participants will be additionally stratified by gender and anxiety score (BAI ≤ 25 vs. > 25). Allocation sequence will not be visible to the psychologists delivering the therapy. Allocation concealment will occur until the participant has been determined eligible for the intervention and sealed envelope reveals to the psychologists which intervention participants have been allocated. Therefore, randomisation will be conducted without any influence of the study team. Psychologists will not be blind to intervention group, due to the nature of the intervention. Whilst they will not reveal to the participant whether the therapy is ADAPT or EFST, due to the nature of the interventions, it is possible participants will not be completely blinded to allocation. A research assistant will be blinded to condition when assessing intervention outcome and questionnaires will be completed without involvement from researchers.

### Data collection

The principal investigator will train the clinical research coordinators, research psychologists and research assistant in data collection, entering, coding and checking as appropriate. Data will be pseudonymised using participant ID. Psychologists will access weekly process data collected prior to therapy sessions starting. The study team will access data using a secure login. Members of the study team will collect interoception data and access this securely. The trained research assistant will assess objective signs of orthostatic intolerance by using a finometer (SMART MEDICAL). Where source data are collected on paper, including the hypermobility (at baseline) and MINI assessments (at baseline and end of intervention), an exact copy of the anonymised data will be manually input into the trial database by a named member of the study team. The research assistant will code all data except treatment allocation group which will be entered by the principal investigator.

Participants will be reimbursed £20 and £25 at the start and end of therapy respectively for completion of trial assessments and to aid retention.

Dropout from the study will be recorded, including reasons where given. Participants are free to withdraw at any point during the study and can request their previously collected data not to be used. Withdrawal or declining to participate will not affect their NHS care in any way; participants are informed of this in the participant information sheet. Participants may be withdrawn from the intervention if their clinical presentation changes in relation to exclusion criteria (e.g. being started on beta-blocker medication, as this could confound the results) or if their clinical condition requires urgent other treatment (e.g. if the participant develops a psychotic disorder). Withdrawn participants will not be replaced.

### Data management

The study team will treat participant information with confidentiality at all times. They will anonymise data held on records and password-protected databases, assign participant ID numbers, and be fully compliant with the General Data Protection Regulation and the Data Protection Act when handling and storing data. Therefore, personal information will be kept separate from the trial data. All members of the research team and other individuals from collaborating trusts or universities involved in collecting, inputting, processing, using and sharing data will have had Information Governance Training. Data management will be a standard item on the agenda for both research team and steering group meetings. Behavioural data will be collected on password protected computers and stored in link-anonymised data files. All data will be backed up to a central storage facility automatically, related to the University of Sussex. Paper files will be kept in locked cabinets.

For statistical analysis, the anonymised data will be downloaded onto password-protected computers. This will be accessible by the trial statistician and principal investigator.

### Statistical methods

Available cases will be analysed following intention to treat principles. The primary outcome will be the BAI which will be compared from baseline assessment to end of therapy. A linear mixed model will be used to test intervention effects, including group comparisons on mean scores of primary and secondary symptom outcome measures. Main effects of condition and time (i.e. repeated measurements) and their interactions will be examined. Effect sizes will be calculated. Missing data will be quantified but no imputation will be performed.

A Data Monitoring Committee has not been arranged, in accordance with the Oxford Clinical Trials Research Unit and the Medicines for Human Use Clinical Trials Regulations (2004); because the intervention occurs over a short period, the protocol will not be modified irrespective of data collected during the intervention and there are minimal risks to participants. No interim analyses are planned.

The independent Trial Steering Committee will help monitor safety (including adverse events), assess adherence to the study protocol and the statistical analysis plan, and oversee progress with data collection. Members include the trial statistician, the PI, the trial consultant clinical psychologist, an independent expert and a patient representative. The principal investigator will regularly conduct data audits to check for possible errors and completeness. If participants or others have concerns regarding the trial conduct, they are advised to contact the Patient Advice and Liaison Service at Sussex Partnership NHS Foundation Trust; this is independent from the investigator and sponsor.

